# Exploring the Influence of a Novel App for Training and Evaluating Walking Aid Skills in Walking Aid Users: Protocol for a Pragmatic Single-Blind Randomized Controlled Trial

**DOI:** 10.2196/71060

**Published:** 2025-12-24

**Keywords:** walking aids, mobile health, mHealth, balance confidence, mobility, randomized controlled trial

## Abstract

**Background:**

More than 12% of the world’s population and more than 1 million Canadians use walking aids to support mobility. Unsafe use of walking aids due to a lack of training may lead to injuries and an increased risk of falls. A novel interactive video-based feedback mobile app to train walking aid fitting and safe use, called ICanWALK (Improving Canadians’ Walking Aid Skills, Learning, and Knowledge), was recently developed.

**Objective:**

The primary objective of this study is to explore the efficacy of the walking aid skills training app on the balance confidence of walking aid users. The secondary objective is to explore the influence of the mobile app on mobility and knowledge of walking aid users.

**Methods:**

A 2-site single-blind pragmatic randomized controlled trial is proposed. A total of 52 adults who use walking aids will be recruited through clinical and community organizations. Participants will complete measures of balance confidence (Activities-specific Balance Confidence scale; the primary outcome), mobility (6-Minute Walk Test and Timed Up and Go test), walking aid skills (Walking Aids Skills Test, WAST), and knowledge of and confidence in walking aid fit and use (self-reported questionnaire) at baseline (T1). Participants will then be randomly assigned to the experimental (ICanWALK app) or attention-matched control group (breathing activity app) and will complete two 20-minute sessions interacting with the assigned app. Participants will be reassessed 2 to 4 days after the intervention (T2) and again 4 weeks later (T3). Analysis of covariance will be performed for primary and secondary outcomes by using SPSS software.

**Results:**

The study protocols were approved by the institutional review boards of both recruitment sites in 2023 and 2024. A feasibility study was conducted from 2023 to 2024 across the 2 sites. As of November 2025, participant recruitment is ongoing and expected to conclude in December 2026. To date, 26 individuals have been enrolled and have successfully completed all 3 assessment time points: T1, T2, and T3.

**Conclusions:**

Using a video-based feedback training approach, a novel app is hypothesized to improve balance confidence, mobility, and knowledge of and confidence in walking aid fitting and use. This structured educational program for fitting and training of walking aids may improve balance confidence. Better walking aid fitting and use may improve mobility, especially for older adults, thereby increasing independence and social participation. Establishing efficacy is an important first step before exploring how the ICanWALK app may be used by walking aid users and clinicians in clinical and community settings.

**Trial Registration:**

ClinicalTrials.gov NCT05347875; https://clinicaltrials.gov/study/NCT05347875

**International Registered Report Identifier (IRRID):**

DERR1-10.2196/71060

## Introduction

Independent personal mobility is associated with physical and psychosocial health benefits, such as reduced risk of chronic diseases, increased participation in meaningful activities, and reduced risk of depression and social isolation [1,2]. Personal mobility, defined as the ability to move oneself (either independently or using assistive devices) within environments [3,4], is a basic human right [3]. According to the Convention on the Rights of People with Disabilities, state parties shall take effective measures to ensure personal mobility with the greatest possible independence [3], which includes facilitating access to quality mobility aids and providing mobility skills training.

The World Health Organization (WHO) and World Bank estimated that 1.3 billion people (representing approximately 15% of the world’s population) experience significant disability, with most of them using walking aids, designed to assist ambulation, such as canes, walkers, crutches, and walking sticks [5,6]. In Canada, walking aids support the independent mobility of more than 1 million Canadians (approximately 4.1% of the population), with a 2% prevalence increase from 2004 to 2012 [7]. Walking aid use is particularly prevalent among older adults [7,8], with approximately 24% of adults aged 65 years and older in the United States and Canada using walking aids [7,8]. With life expectancy rising worldwide, the population older than 65 years is expected to continue to increase [9], and, consequently, the need for walking aids will also increase [10].

When used appropriately, walking aids can significantly enhance perceived balance confidence in individuals with mobility challenges, especially older adults and those with neurological conditions [11]. Improved balance confidence has been shown to facilitate motor performance, leading to smoother and more efficient movements [12,13]. Walking aids support postural stability, compensate for muscle weakness or motor deficits, and off-load weight from an injured or postoperative lower limb [12]. Their use is associated with greater feelings of safety, which may contribute to a higher level of physical activity, independence, and reduced risk of fall-related injuries [13,14]. Overall, walking aids support mobility [15], encourage participation [11], and offer both physical and psychosocial benefits [16].

Notwithstanding the numerous benefits of walking aids, inappropriate fit and unsafe use can lead to discomfort, pain, injuries, and even an increased risk of falls. A recent review identified an increased risk of injury when crutches were poorly fitted and used improperly due to a lack of training before use [17]. Inadequate use of walking aids was also found to be associated with a greater risk of falls [15,18]. In US emergency departments, 47,312 fall-related injuries among older adults, which were associated with walking aids (87.3% with walkers, 12.3% with canes, and 0.4% with both), were treated annually between 2001 and 2006 [19]. Furthermore, high rates of walking aid disuse or dissatisfaction were associated with difficult or risky use due to a lack of training before prescription [20]. Although injuries and fall risks could likely be reduced through better education and training, no standardized training program has been documented. A recent study by Best et al [21] that documented the quality of existing online educational resources for mobility device training showed that most walking aid training was in the form of infographics and basic instructions and was not evidence based. Most people obtain walking aids independently from the pharmacies or clinics without receiving instruction or demonstration [20,22]. A standardized and effective approach to training walking aid skills may enhance balance confidence and mobility while reducing the risk of injuries and falls for walking aid users and may be useful for health care professionals (as they are the primary source of care for patients).

The use of mobile apps is increasingly widespread and recognized for improving health outcomes in the general population [23] as well as in individuals with chronic diseases [24]. The COVID-19 pandemic also facilitated the use of mobile health (mHealth) for providing some health services and reducing initial preoccupations about safety, which has increased accessibility to health care services and education while reducing geographic and transportation barriers [24]. While educational mHealth apps have demonstrated potential in enhancing health-related knowledge and promoting behavior change [25-28], their overall effectiveness remains inconsistent. This variability is largely attributable to differences in the integration of key design and theoretical elements, such as behavior change techniques, personalization, user-centered design, social support features, evidence-based content, and technical reliability [29-32]. In the specific context of rehabilitation, some apps incorporate video-based instructional content; however, they typically offer passive viewing experiences and lack interactive features that support active skill acquisition [25,33-35]. Critically, few enable users to engage in guided practice with real-time or postexercise feedback that facilitates the detection and correction of performance errors by comparing their movements to a model [36]. Moreover, the use of video-based feedback, an evidence-informed strategy grounded in observational learning theory, remains notably underused, despite its potential to enhance motor skill acquisition, user engagement, and self-efficacy [37,38]. In addition, no educational app for teaching the fitting and safe use of walking aids exists to date.

The ICanWALK (Improving Canadians’ Walking Aid Skills, Learning, and Knowledge) mobile app was developed to address critical gaps related to walking aids, including improper fitting, unsafe use, and the widespread lack of structured training [39]. The ICanWALK app is a video-based feedback and interactive tool aiming to serve as a large-scale educational tool [39]. A recent pilot experimental study involving 13 walking aid users reported a high rate of usability (88%) and acceptability of this novel app [40]. Participants found the app simple, useful, and easy to use [40]. This study also showed improvement in balance confidence after two 15-minute sessions using the ICanWALK program [40]. Hence, this study will explore the efficacy of the ICanWALK program on the primary outcome of balance confidence in adult walking aid users. We hypothesize that exposure to the app’s content (video-based feedback and interactive learning) will lead to improved balance confidence (main variable), and we expect that if balance confidence improves, mobility and walking aid skills (secondary outcomes) will also improve.

## Methods

### Study Design

This study will use an assessor-blind, 2-site parallel-group, randomized controlled trial (RCT). This study protocol was registered on ClinicalTrials.gov (NCT05347875). The SPIRIT (Standard Protocol Items Recommendations for Intervention Trials) guidelines [41] and the CONSORT (Consolidated Standards of Reporting Trials) statement [42] will be followed.

### Participants and Recruitment

To be included in this study, participants should be aged 18 years or older, should use a walking aid (cane, crutch, or walker) for at least 75% of ambulatory time (self-reported), and should be able to communicate in English or French. Participants will be excluded if they have a progressive condition or injury that may restrict or be worsened by walking aid use (self-reported) or a visual impairment that could limit their ability to interact with a mobile app (self-reported). Reasons for exclusion, declining participation, and dropout will be documented for CONSORT purposes (Figure 1) [33,42].

Participants will be recruited from clinics, community centers, semiprivate assisted living facilities, and via social media and emails distributed to health care practitioners by the study coordinators (FN and [name]). Recruitment posters will be distributed, and emails will be sent to community associations and organizations, practitioners (kinesiologists, physiotherapists, and occupational therapists) in contact with walking aid users, and all university and research center networks. Active approaches, such as community meetings with presentations and collaboration with community partners in identifying potential participants, will also be used. The study coordinators from the 2 sites (FN for Québec and [name] for Calgary) will contact interested, eligible participants via email and telephone and send them a consent form at least 24 hours before the first evaluation.

**Figure 1 figure1:**
[figure not shown]
Flow diagram of the progress through the phases of a parallel randomized controlled trial of 2 groups.

### Sample Size

The sample size calculation was based on the Activities-specific Balance Confidence (ABC) scale questionnaire (primary outcome) [43]. No study has reported the minimum clinically important difference for the ABC scale among walking aid users. However, considering a study on 376 patients with knee osteoarthritis who had undergone surgery (many of whom used a walking aid), ABC scores increased by an average of 9.2% 1 year after total knee arthroplasty (repeated measures model; Cohen *d*=0.59) [44]. On the basis of the variability reported in the study [44], an estimated correlation of 0.5 between measurements, including ABC scale and 2 potential covariates (type of walking aid and duration of walking aid use), a sample size of 45 would be sufficient to explore a 2-way difference between groups (*F* tests) in a 2-way repeated measures model (2 groups×2 time points; 1–β=.9; α=.05; G*Power [Heinrich Heine University Düsseldorf]) [45]. With a conservative dropout rate estimated at 15% [46], a total sample size of 52 participants is enough to find significant differences between groups for the primary outcome. To minimize participant dropout and ensure high retention rates, several strategies will be implemented. These include clear and transparent informed consent procedures, regular and supportive communication with participants, and flexible scheduling for study visits. Efforts will be taken to maintain a strong and supportive relationship between the research team and participants. All participants will be reassured about the confidentiality of their data and the importance of their contribution to the success of this study.

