### Outcomes

#### Primary Outcome

Given the ICanWALK app’s theoretical grounding in self-efficacy, behavior change, and skill acquisition, balance confidence—assessed with the ABC scale—was selected as the primary outcome due to its direct relevance to the intervention’s mechanisms of action [32,43]. The ABC scale offers a validated, context-specific measure of individuals’ perceived confidence in performing daily mobility tasks with a walking aid, capturing both psychological and functional dimensions of change [43]. As such, it serves as a sensitive and theoretically congruent indicator of the intervention’s anticipated impact. The ABC scale is a 15-item self-assessment measure that asks individuals to rate their confidence in balance while performing a series of activities on a scale ranging from 0 (no confidence) to 45 (total confidence) [43]. The raw scores are converted into percentages by dividing the sum of the individual scores by the total score and then scores ranging from 0 (no confidence) to 100% (total confidence). The ABC scale is reliable in individuals using mobility devices [51], healthy older adult community dwellers [52], individuals who have undergone lower limb amputation [51,53], individuals with Parkinson disease [54] or knee osteoarthritis [55], stroke survivors [56], and those with traumatic brain injury [57]. The ABC scale is highly sensitive to fall risk [58]. Previous studies have demonstrated high test-retest reliability (intraclass correlation [ICC]=0.85) and excellent construct validity (*r*=0.60-0.75) with the Berg Balance Scale, Community Balance and Mobility Scale, and TUG test [52,55,56]. The administration time is 10 to 15 minutes.

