### Statistical Analysis

Responses to questionnaires and test scores will be imported from the LimeSurvey platform and compiled into a Microsoft Excel file. Descriptive statistics (means, SDs, frequencies, and percentages) will be used to summarize sociodemographic data.

An analysis of covariance will be performed to detect postintervention differences between groups for the primary and secondary measures using the respective T1 score as the covariate. Dropout rates and reasons will be reported. Depending on the nature of the missing data (proportion of missing values), appropriate methods will be chosen with careful consideration of the data structure and the underlying assumptions. The significance level will be set at .05, and all statistical tests will be 2-tailed. The scores from the self-reported questionnaires on walking aid knowledge and confidence will be summed and analyzed using an appropriate parametric test (if normally distributed). Retention of balance confidence, mobility, and self-reported score of knowledge in the experimental group will be evaluated using 2-tailed paired *t* tests. Sensitivity analyses will also be conducted based on walking aid type, walking aid use experience, previous training, and the main reason for use. All analyses will be performed in SPSS software (version 27; IBM Corp).

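### At the protocol's own d of 0.59 and correlation of 0.5, the planned baseline-adjusted ANCOVA has about 61% power with 45 analysed, not the stated 90%

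*Protocol article*

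**What the plan says.** The Sample Size section takes its effect from a cohort of patients after knee surgery: "ABC scores increased by an average of 9.2% 1 year after total knee arthroplasty", labelled "repeated measures model; Cohen *d*=0.59". It adds "an estimated correlation of 0.5 between measurements", gives no source for that value, and sets "1–β=.9; α=.05". From a model with two groups and two time points it arrives at 45 participants, raised to 52 for 15% dropout.

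The Statistical Analysis section compares the groups after the intervention by ANCOVA, "using the respective T1 score as the covariate", and states that "all statistical tests will be 2-tailed".

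The Primary Outcome section reports for the same scale "high test-retest reliability (intraclass correlation [ICC]=0.85", drawn from previous studies. The article does not relate this figure to the 0.5.

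The Abstract's Results paragraph says that "26 individuals have been enrolled and have successfully completed all 3 assessment time points". Recruitment is to run to December 2026.

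**The concern.** In an ANCOVA on the baseline score, the T1-T2 correlation r sets the residual variance, which is proportional to 1 − r². That is 0.75 at r = 0.5 and 0.2775 at r = 0.85, a ratio of 2.7. The correlation is therefore a leading input to the power of the planned test. The protocol gives it as 0.5 without a source, in a calculation for another model.

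The sessions fall within one week and T2 follows 2 to 4 days later, so a correlation above 0.5 is plausible, although the time from T1 to the first session is not stated. What is at stake is the claim that 52 participants are enough for the primary outcome. A reader who takes the 90% at face value would expect more of the trial than the planned test delivers at the stated inputs.

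**Working it through.** **Inputs.** d = 0.59, r = 0.5, α = .05 two-sided, power 0.90 and 45 analysed (Sample Size; Statistical Analysis); 1:1 allocation (Randomization and Allocation); ICC 0.85 (Primary Outcome); 26 completers (Results). The source study's SD is not given. If 9.2 points corresponds to d = 0.59, the SD is 9.2/0.59 = 15.6 points, but the text does not say whether this is the SD of scores or of changes.

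**Step 1: the plan's own 45.** With f = d/2 = 0.295 and r = 0.5:
- Group-by-time interaction, λ = f²·N·2/(1 − r), df 1 and N − 2: N = 33 for 90% power.
- Between-groups effect, λ = f²·N·2/(1 + r), df 1 and N − 2: N = 93.

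Neither gives 45. The figure 45 does appear for the interaction at r = 0.5 if f = 0.25 is entered (power 0.906), but that f is not stated.

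**Step 2: the planned ANCOVA at the stated inputs.** λ = (d²·N/4)/(1 − r²), df 1 and N − 3. With N = 45: d²·N/4 = 0.3481 × 45/4 = 3.916, and λ = 3.916/0.75 = 5.22. Against the critical value F(1, 42) = 4.07 the power is 0.61. Power reaches 0.90 at N = 93. If all 52 were analysed, power would be 0.67.

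**Step 3: which SD.** The SD of change equals the raw SD × √(2(1 − r)). At r = 0.5 the factor is √1 = 1, so the 61% and the 93 do not depend on the reading of d. At other values of r they do. If d is in change-score SDs, the raw-score effect is 0.59 × √(2(1 − r)), which is 0.323 at r = 0.85.

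| r | Power at 45, d in raw SDs | N for 90% | Power at 45, d in change SDs | N for 90% |
|---|---|---|---|---|
| 0.5 | 0.61 | 93 | 0.61 | 93 |
| 0.7 | 0.77 | 64 | 0.55 | 105 |
| 0.8 | 0.90 | 46 | 0.53 | 111 |
| 0.85 | 0.96 | 36 | 0.52 | 114 |

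On the raw-SD reading, 45 reaches exactly 90% at r = 0.803.

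**Step 4: difference detectable with 90% power at 45, raw-SD reading.** At r = 0.5 it is 0.857 SD × 15.6 = 13.4 points; at r = 0.85 it is 0.521 SD × 15.6 = 8.1 points. The 9.2-point reference lies between the two.

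**Step 5: what 26 pairs can show.** Fisher z with standard error 1/√23 gives these 95% confidence intervals: 0.14 to 0.74 if the observed r is 0.5, 0.43 to 0.86 if it is 0.7, and 0.69 to 0.93 if it is 0.85. The last two contain 0.80. On the raw-SD reading, an observed 0.85 is compatible with a required N anywhere from 66 down to 19.

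**The case against.** **The two correlations contradict each other.** A reader might infer this from 0.5 in one section and 0.85 in another. The documents do not support it. The 0.85 is retest reliability in other populations; the 0.5 is a planning value across an intervention in a mixed sample of walking aid users. The wording around the 0.5, which also mentions two covariates, leaves open which correlation is meant.

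**0.5 is the cautious choice.** With d fixed in raw-score SDs, a higher r lowers the required N for ANCOVA, so choosing 0.5 over 0.85 does not by itself make the trial too small. This stands. But the cautious value gives 93 for the planned test, not 45.

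**In an interaction model 45 is enough.** With f = 0.295, interaction power at 45 is 0.97 at r = 0.5 and above 0.99 at 0.85. However, in that test f = 0.25 equals a between-group difference in change of 1.0 raw SD, so f = 0.295 equals 1.18 SD, twice the stated d. With d = 0.59 as the difference in change, f is 0.1475 and power at 45 is 0.49 at r = 0.5 and 0.94 at r = 0.85.

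**The effect size matters as much as r.** This stands. On the raw-SD reading at r = 0.85, power at 45 is 0.70 for d = 0.4 and 0.46 for d = 0.3. The d itself is a one-year change within a surgical cohort, used here for a contrast between groups. It would be wrong to say that the correlation alone decides whether 45 suffices.

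**The final result does not depend on the planning value.** Also true: the ANCOVA confidence interval will use the observed residual variance. The point concerns the stated power, not the validity of the analysis.

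**Conclusion.** The stated 90% power does not follow for the planned analysis. At d = 0.59 and r = 0.5 the T1-adjusted ANCOVA has about 61% power with 45 analysed and needs 93 for 90%, on either reading of d. That is the firm part, with d taken as a between-group effect.

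What happens above r = 0.5 depends on an SD that the document does not give. In raw-score SDs, power is 77% at r = 0.7, 90% at 0.80 and 96% at 0.85, so the claim holds only if r is about 0.80 or more. In change-score SDs, power stays at 52% to 61%. The cited ICC makes a value above 0.5 plausible and establishes no more than that.

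A reader might also infer that the 26 completers can resolve the matter now. They cannot: an observed 0.85 has a confidence interval that spans the 0.80 threshold, and a correlation says nothing about the true effect.

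**What to change.** In the Sample Size section:
- Keep 0.5 on record as the value on which the trial was sized, and say where it came from.
- State the SD, and whether d = 0.59 refers to raw scores or to changes.
- Give the power at 45, or the difference detectable with 90% power, for the planned T1-adjusted ANCOVA over r = 0.5 to 0.85.
- Say in one sentence how the retest ICC in the Primary Outcome section bears on that range.

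Optionally, add an estimate of r and the SD from the 26 completers, pooled over arms without any look by arm and reported with its confidence interval. Pooling distorts little: if the true effect is 0.59 raw SDs, the pooled correlation is r/√(1 + 0.59²/4), which takes 0.50 to 0.48 and 0.85 to 0.82.

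The cost is a short calculation and a few rewritten sentences. It needs no added participants and has no cost in type I error, because only pooled nuisance parameters are used. The downside is that the stated power probably becomes less favourable.

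### The 90% power stated for 45 analysed participants cannot be reproduced from d = 0.59, the only effect size given; read as a between-group difference at r = 0.5, it gives the planned ANCOVA about 61%

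*Protocol article*

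**What the plan says.** The Sample Size section notes that no minimum clinically important difference for the ABC scale is known in walking aid users. It turns to a knee-surgery cohort of 376 patients, in which "ABC scores increased by an average of 9.2% 1 year after total knee arthroplasty", reported with a Cohen d of 0.59. To this it adds "an estimated correlation of 0.5 between measurements" and two potential covariates, walking aid type and duration of use. It concludes that "a sample size of 45 would be sufficient to explore a 2-way difference between groups", by F tests "in a 2-way repeated measures model (2 groups×2 time points; 1–β=.9; α=.05". Allowing for 15% dropout, it then says that "a total sample size of 52 participants is enough to find significant differences between groups for the primary outcome".

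The Statistical Analysis section plans something different from a repeated measures model: "An analysis of covariance will be performed to detect postintervention differences between groups for the primary and secondary measures", with the T1 score as covariate and 2-tailed tests at .05. Allocation is 1:1. The article gives no between-group effect, no SD, no Cohen f and no R-squared for the covariates.

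**The concern.** Two things do not fit. First, the only effect size is a before-and-after change in a single group over a year following surgery, but it is used to justify a comparison between two attention-matched arms after two short app sessions. Second, 0.59 SD is a moderate difference, and 45 participants in two groups looks too few to detect it with 90% power at a correlation of 0.5.

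At stake is how the primary result is read. If power for the quoted effect is nearer 60% than 90%, about 4 in 10 such trials would miss an effect of that size, and the stated 90% would give a non-significant result more weight against the app than it deserves.

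**Working it through.** **Inputs.** From Sample Size: d = 0.59, mean change 9.2 points, r = 0.5, power .90, alpha .05, 2 groups × 2 time points, 45 analysed, 52 enrolled, 15% dropout. From Statistical Analysis: ANCOVA on T1, 2-tailed. From Randomization and Allocation: 1:1. Implied, not stated: SD = 9.2/0.59 = 15.6 points.

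**Trying to reproduce 45.** For a 2 × 2 repeated measures design, the noncentral F parameters in G*Power form are:
- between-group test: λ = f²·N·2/(1 + r)
- group-by-time interaction: λ = f²·N·2/(1 − r)

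The last column gives the size of difference that each entry implies.

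| Test and entry | N for 90% | Power at 45 | What the entry implies |
|---|---|---|---|
| Between-group, f = d/2 = 0.295 | 93 | 61% | 0.59 SD between groups |
| Interaction, f = d/4 = 0.1475 | 123 | 49% | 0.59 SD difference in change |
| Interaction, f = d/2 = 0.295 | 33 | 97% | 4 × 0.295 = 1.18 SD difference in change |
| Interaction, f = 0.25 | 45 | 90.6% | 4 × 0.25 = 1.0 SD difference in change |
| ANCOVA, 2 covariates, f = 0.5 | 45 | 90.6% | 1.0 residual SD, about 0.87 raw SD at r = 0.5 |

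A one-group paired test at d = 0.59 needs 33. Entering 0.59 itself as f gives 25 (between-group) or 10 (interaction). So 45 arises only from effect sizes that the protocol does not state. In points, with SD 15.6, the f = 0.25 interaction corresponds to about 15.6 and the f = 0.5 ANCOVA to about 0.866 × 15.6 = 13.5, against the 9.2 cited.

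**The planned ANCOVA.** Adjusting for T1 reduces the SD by √(1 − r²) = √0.75 = 0.866, so the standardised effect is 0.59/0.866 = 0.681.
- N = 45 (22 and 23): noncentrality = 0.681 × √(22 × 23/45) = 2.28 on 42 df; power 60.7%.
- N = 52: noncentrality 2.46; power 67.3%.
- N = 93: power 90.1%; N = 92 falls just short at 89.8%.

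**What 45 can detect.** 90% power at N = 45 needs d = 0.857, or 0.857 × 15.6 = 13.4 points (52 analysed: about 12.4 points). The expected 95% CI half-width at N = 45 is 2.018 × 15.6 × 0.866 × √(1/22 + 1/23) = 8.1 points.

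**Sensitivity to the correlation, N = 45.**

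| r | d in raw-SD units | d in change-SD units |
|---|---|---|
| 0.5 | 61% | 61% |
| 0.7 | 77% | 55% |
| 0.8 | 90% | 53% |
| 0.85 | 96% | 52% |

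The columns agree at r = 0.5 because the change-score SD, √(2(1 − r)) raw SDs, then equals the raw SD. In the second column the raw effect is 0.59 × √(2(1 − r)).

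**Covariates.** To reach 90% at N = 45 with d = 0.59, all covariates together must explain about 64.5% of the variance. T1 at r = 0.5 explains 25%, so the other two would have to add about 40 percentage points.

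**Dropout.** 45/0.85 = 52.9, that is 53; 45 × 1.15 = 51.75, that is 52. The one-participant difference is immaterial.

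**The case against.** The strongest reply is that the protocol never says 0.59 was entered as the between-group effect. It bases the calculation on the variability in the cited study and does not disclose the f used. That stands: the safe statement is that 45 cannot be reproduced from the only effect size given, and that 61% is what follows if that effect is read as a between-group difference. A reader might go further and infer that f = 0.25 was the entry. The match is exact, but the documents do not say so, and it remains a guess.

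A second reply is that the named model fits G*Power's interaction test, where f = d/2 = 0.295 needs only 33 and makes 45 ample. The arithmetic is right, but that entry describes a 1.18-SD difference in change, twice the cited effect, so it does not support 90% power for 0.59.

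Third, r = 0.5 may be pessimistic. The Primary Outcome section cites a test-retest ICC of 0.85, and T2 follows the sessions by only 2 to 4 days. This also stands in part: at r = 0.8, with d in raw-SD units, power is about 90%. So a reader should not conclude that the trial's true power is 61%. But 0.5 is the value the protocol chose, and if d was standardised by the change SD, a higher correlation lowers power.

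The two potential covariates do not help: no R-squared is given, and the Statistical Analysis section names only the T1 score for adjustment.

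Finally, the Discussion calls the trial exploratory. That argues against demanding more participants; it does not make an explicit 90% claim correct.

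**Conclusion.** The point holds. The 90% power claim, and the statement that 52 suffices for significance, are not supported by the figures printed beside them. For d = 0.59 as a between-group difference, r = 0.5 and two-sided alpha .05, the planned ANCOVA has about 61% power at 45 analysed and 67% at 52, and about 93 would be needed for 90%. The result rests on three things: reading 0.59 as a between-group difference (the article offers no other effect), the protocol's own correlation, and, for figures in points, a back-calculated SD of 15.6.

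Separately from the arithmetic, the cited effect is uncontrolled, so it says little about the difference to expect between two arms.

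A reader might infer that the trial must enrol about 93 or more. The documents do not support that: the trial is described as exploratory, no minimum important difference is available, and recruitment is under way, with 26 participants having completed all assessments by November 2025. What is wrong is the stated power, which should be corrected before results are read against it.

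**What to change.** Keep 52 participants and rewrite the Sample Size text:

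1. Report the G*Power test, the value of f and the options actually used.
2. Restate the power for the analysis that will be run, for example: *With 45 analysed, an assumed T1–T2 correlation of 0.5 and an assumed SD of 15.6 points (9.2/0.59, to be checked against the cited study), ANCOVA on T1 has about 61% power for a 9.2-point between-group difference and 90% power for about 13.4 points; the expected 95% CI half-width is about 8 points.*
3. State that 9.2 points is an uncontrolled before-and-after change, not a difference between randomised arms.
4. Delete the statement that 52 is enough to find significance, and base the conclusion on the estimated difference and its confidence interval.

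This costs a rewording and a check of the cited study. It needs no extra participants; the downside is a less favourable stated power.

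### At the stated 15% dropout, 52 recruits leave about 44 completers, one short of the 45 the plan requires: a minor error in the sample size sentence

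*Protocol article*

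**What the plan says.** The Sample Size section of the protocol article gives the calculation in two steps.

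- Before dropout: "a sample size of 45 would be sufficient to explore a 2-way difference between groups", in a repeated measures model with 2 groups and 2 time points, at "1–β=.9; α=.05", with "an estimated correlation of 0.5 between measurements".
- After dropout: "With a conservative dropout rate estimated at 15" per cent, the section concludes that "a total sample size of 52 participants is enough to find significant differences between groups for the primary outcome".

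The Methods paragraph of the abstract repeats the target: "A total of 52 adults who use walking aids will be recruited". The order of the two steps makes 45 the number needed for analysis and 52 the number to recruit. The article does not say how 45 and 15% were combined to give 52.

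**The concern.** A dropout allowance should ensure that the number left after the assumed losses is at least the number the power calculation needs. Here it falls just short: applying the plan's own 15% to its own 52 gives fewer than 45. The discrepancy does not depend on whether the effect size is well chosen, because it uses only the three figures in the paragraph.

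What is at stake is mainly the accuracy of the justification. The final report will have to restate it, and any reader can repeat the division. The effect on power has to be worked out before the discrepancy is given any weight.

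**Working it through.** **Inputs, all from the Sample Size section unless noted**

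- Required for analysis: 45
- Dropout: 15%
- Recruitment target: 52 (also in the abstract)
- Power 0.90, α = 0.05, correlation 0.5 between measurements, 2 groups × 2 time points
- Two-sided testing, from Statistical Analysis ("all statistical tests will be 2-tailed")

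**Step 1. Reproduce 52.** Multiplying, 45 × (1 + 0.15) = 51.75, which rounds up to 52. Dividing, 45/(1 − 0.15) = 52.94, which gives 52 only if rounded down. The first route is the likelier one. Neither is shown in the article.

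**Step 2. Number needed at 15% dropout.** N × 0.85 ≥ 45 requires N ≥ 52.94, so N = 53. Check: 53 × 0.85 = 45.05.

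**Step 3. What 52 delivers.** 52 × 0.85 = 44.2 expected completers, 0.8 below 45. The number that can be lost while keeping 45 is 52 − 45 = 7, and 7/52 = 13.5%.

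**Step 4. Cost in power.** The article does not state the effect size f that was entered in G*Power. It gives only the source: "ABC scores increased by an average of 9.2% 1 year after total knee arthroplasty", with Cohen d = 0.59. I therefore used values of f that reproduce 45. The test is the group-by-time interaction, with

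λ = f² × N × m/(1 − ρ), m = 2, ρ = 0.5, on 1 and N − 2 degrees of freedom.

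| Setting (assumed) | Power at 45 | Power at 44 | Loss |
|---|---|---|---|
| f = 0.25 (45 is the smallest N reaching 0.90) | 0.906 | 0.8997 | 0.7 points |
| f = 0.247 (power exactly 0.90 at 45) | 0.900 | 0.893 | 0.7 points |

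For f = 0.25, λ = 0.0625 × 45 × 2/0.5 = 11.25 at 45 and 0.0625 × 44 × 2/0.5 = 11.0 at 44. Halving d = 0.59 to f = 0.295 gives N = 33 for this test. It does not reproduce 45 and was not used.

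**The case against.** Four arguments limit the point.

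1. **No formula is stated.** A reader might infer that the plan multiplied by 1.15. The numbers fit that, but 52.94 rounded down also gives 52, so the documents do not establish it. The objection stands as to the mechanism. It does not affect the result, since 52 is one short by either route.

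2. **The sentence claims that differences can be found, not that 45 will complete.** With 44 completers, power is still about 0.89 to 0.90. A reader might conclude that the claim of sufficiency is false and the trial underpowered for this reason. The calculation does not support that. What fails is only the match between 45, 15% and 52.

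3. **The planned analysis leaves room.** Statistical Analysis specifies analysis of covariance on the T1 score, not the repeated measures interaction. At a correlation of 0.5 the residual variance is 1 − 0.5² = 0.75 of one measurement's variance, against 2 × (1 − 0.5) = 1.0 for a change score. For the same assumed effect (f = 0.25 in the interaction test), power at 44 is about 0.96. This stands, provided that the effect and correlation are as assumed.

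4. **Retention so far looks better than 15%.** If every recruit independently has a 15% chance of dropping out, the chance of at least 45 completers from 52 is 47%, and it is tempting to read that as a likely failure. But the Results section reports 26 participants who were recruited and completed all three assessments. If they are everyone enrolled so far, 15% loss among the other 26 leaves 26 + 22.1 = 48.1, and the chance of at least 45 is about 97%. The text does not settle whether those 26 are all who enrolled, so this is conditional. In either case 45 is not a cliff: missing it by one costs less than one point of power.

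Arguments 2 to 4 show that the practical harm is negligible. They do not make the three stated figures agree. The article rests its target on 15%, not on the retention observed or on the efficiency of the covariance analysis.

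**Conclusion.** The sample size sentence is wrong by its own inputs, and the error is minor. At 15% dropout, 45 analysable participants need 53 recruits; 52 leaves an expected 44.2 and covers dropout only up to 13.5%. This part rests on no outside assumption. The size of the consequence rests on an assumed f near 0.25, chosen because it reproduces 45: the loss is about 0.7 percentage points of power. Neither the validity of the trial nor its recruitment target is in question on this ground. Going to 54 to keep the arms equal would be a preference; 52 already divides into 26 and 26.

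**What to change.** Reword one sentence in Sample Size, in either of two ways:

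- state that 52 participants allow for about 13.5% dropout (7 of 52); or
- keep 15%, state that about 44 completers are expected, and give the power at 44 with the effect size f that was used.

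The abstract can keep its figure of 52. The cost is one sentence, and no change in enrolment is required.
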